#### Care management

The care management intervention seeks to address blood pressure management by providing patient education, promoting self-management behaviors, and introducing organizational change. Poor adherence to medications [24], limited access to healthful foods [25], and poor quality diets [26] contribute to racial disparities in blood pressure control. The care management team aims to reduce disparities and achieve guideline concordant care through the promotion of self-management skills and medication titration.

Patients with a diagnosis of hypertension (ICD9 codes) and with their most recent blood pressure ≥140/≥90 mmHg are eligible for care management services. Care managers (either RDs or PharmDs) review the clinic’s electronic patient registry, which abstracts data from the practice’s EMR, to identify eligible patients to outreach via telephone. Providers in the clinic also refer eligible patients directly to the care managers for care management services. Eligible patients receive three sessions totaling 120 minutes with an RD and/or a PharmD (Figure 2). The RD covers lifestyle behaviors related to the management of hypertension including the DASH diet, weight loss, and exercise. The PharmD addresses issues related to medication adherence and titration, if necessary. Embedding care managers in the clinic allows for additional patient counseling and enhances providers’ ability to address patients’ complex needs.

**Figure 2 F2:**
[figure not shown]
Project ReD CHiP’s flowchart for patients in care management.

Recognizing the effectiveness of motivational interviewing in promoting health behavior change [31,32], medication adherence [33], and health outcomes [31-33] in African Americans, our care managers utilize motivational interviewing techniques to assess patients’ knowledge of hypertension, current self-management practices, barriers to self-management, and individual preferences in managing hypertension. Additionally, the care managers provide education and recommendations specific to patients’ needs, preferences, and cultural context through the use of customizable, literacy-sensitive modules about blood pressure management. The care managers also utilize a community resource guide to help address the environmental determinants of disparities. Delivery of culturally and linguistically tailored health information increases the acceptability of interventions in minority populations [35].

#### Provider education

The provider education intervention aims to improve blood pressure control and reduce disparities by delivering individualized performance feedback and introducing additional provider-tailored educational resources. It has been shown that PCPs use less patient-centered communication in visits with African American patients [27,28], and patients with low health literacy ask their physicians fewer questions [29]. In developing this intervention, we recognized that the combination of race stratified performance reports and cultural competency training increases clinician awareness of disparities in care [34] and thus incorporated these strategies.

Through this intervention providers are given access to a web-based dashboard that imports clinic measurements and patient information from the EMR. The dashboard increases providers’ awareness of disparities by identifying the percentage of their patients achieving guideline-concordant hypertension control overall as well as among their African American and white patients.

To advance providers’ patient-centered communication skills we developed a training website containing a series of ultra-brief (approximately 30 second) video demonstrations of targeted skills using simulated patient-provider interactions. A pilot study using this approach found that clinicians reported significant changes in routine use of demonstrated skills even after less than 15 minutes of exposure to the website [39]. Moreover, in earlier work we found that providing clinicians with communication skills training can reduce disparities and improve patient-reported outcomes and blood pressure control in ethnic minorities [36]. The videos illustrate a variety of assessment and partnership skill examples to improve the patient-provider encounter and promote patient adherence. A variety of patient scenarios are presented and the videos demonstrate methods to help providers address individual and environmental determinants of disparities. Prior to viewing the video clips, providers complete a self-assessment regarding their use of specified communication behaviors during visits with uncontrolled hypertensive patients. Immediately after viewing the skills videos, they are asked to complete a short survey regarding their intention to use the demonstrated communication techniques. Six months after their first use of the website, physicians are contacted again and asked to report on their use of specified communication behaviors and encouraged to return to the website.

### Data collection, outcome measures, and statistical analysis plan

#### Data collection

Prior to implementation, PCPs and MAs at each clinic completed a ‘motivation survey’ to assess several areas of focus relevant to the acceptance and implementation of the interventions. The areas of focus included respondents’ readiness to change; perception of barriers to safety/quality and addressing healthcare disparities; perception of workflow and organizational stress; medication prescription practice; and how respondents felt the interventions would affect the care they provide to their patients. To better assess organizational functioning and examine how perceptions of the organization’s teamwork and safety culture could influence the interventions, we created an ‘organization survey’ by adding questions to the Safety Attitude Questionnaire [40], which JHCP administers annually to all providers and staff. These survey responses have been used to describe the baseline organizational environment at each of the six clinic sites.

In the care management intervention, after patients attend three visits with the care managers they will complete surveys to assess their experiences with the program. Additionally, at two time points throughout the study we are conducting a patient survey at two of the participating clinics. We will anonymously survey 210 hypertensive patients in the waiting room at each of the selected sites. The responses will help assess the impact of the intervention on patient-reported outcomes, including patient knowledge, attitudes, experiences of care, and self-reported behaviors at each site.

#### Outcome and process measures

We are retrospectively extracting a range of process and outcome measures (already collected by the clinics) from JHCP’s EMRs (Table 5). We are collecting aggregate data at the system, clinic and provider levels. Data will be expressed as an aggregate percentage for a time period of one week, with the denominator equal to the number of patients seen in clinic by all PCPs that week and the numerator equal to the number of patients that achieved the measure as defined in Table 5. Race/ethnicity, gender, age, and presence of other chronic illnesses (diabetes, chronic kidney disease, coronary artery disease) categories will be extracted and the aggregate data will be stratified by these categories. Race/ethnicity is self-reported at the initial clinic visit.

**Table 5 T5:** Process and outcome measures used in Project ReD CHiP

**Type**	**Measure+**	**Notes and definitions**
Primary process measure	% with uncontrolled BP with medication titration in last 3 months	Uncontrolled BP ≥140/≥90 (or ≥130/≥80 if DM or chronic kidney disease); titration can be dose increase or medication change/addition
Secondary process measures	% with BP measure in EMR in last 12 months	
	% with history of pre-HTN with BP measure in last 12 months	Two clinic BPs ≥120-<140≥80-<90; not on HTN medication
	% with HTN with measure in last 6 months	Two clinic BP ≥140/≥90 OR use of a HTN medication OR ICD9 diagnosis (401.xx)
	% with HTN on a thiazide diuretic	
	% with HTN and DM on ACE-I or ARB	DM defined by ICD9 code 250.xx
	% with lipid panel performed in last 5 years^*^	May not be possible as EMR only in all clinics since March 2006
	% with BP≥135/≥85 screened for DM in last 5 years^*^	May not be possible as EMR only in all clinics since March 2006
Implementation uptake process measures	% with BP measured with OMRON	
	% of SBP and DBP measures ending in zero	
	% of eligible patients enrolled in care management	
	% completion rate for those enrolled in care management	
	Provider behavioral intention related to assessment and partnership skills	Measured at completion of the website review and at 6 months post-intervention
	Change in provider self-reported use of assessment and partnership behaviors	Measured before the website review and at 6 months post-intervention
	% of providers receiving web training at each site	Measured at 6 months post-intervention
	Provider self-reported use of HTN dashboard	Measured at 6 months post-intervention
Primary outcome measure	% with controlled BP	Controlled BP defined as <140/<90 (or <130/<80 if DM or chronic kidney disease present)
Secondary outcome measures	% with controlled LDL	Controlled LDL defined as <130 (or <100 if DM or coronary artery disease)
	% with controlled HDL	Controlled HDL defined as >50 in women or >40 in men
	% with controlled triglycerides	Controlled triglycerides defined as <150
	% with controlled A1C	Controlled A1C defined as <7.0
	Mean SBP, DBP, LDL, HDL, triglycerides, A1C	

+Data are aggregated in one week intervals at baseline, during and after intervention roll-out for a minimum of 24 weeks.

*These measures will only be performed in clinics that have had the EMR system in place for at least 5 years.

Abbreviations: *%* percent, *BP* blood pressure, *DM* diabetes mellitus, *EMR* electronic medical record; *HTN* hypertension, *ACE-I* angiotensin converting enzyme inhibitor, *ARB* angiotensin receptor blocker, *SBP* systolic blood pressure, *DBP* diastolic blood pressure, *LDL* low density lipoprotein, *HDL* high density lipoprotein, *A1C* glycated hemoglobin.

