## Methods

### Study design and specific aims

#### Specific aims

This ongoing study has three specific aims, which are reflected in Table 1 with associated hypotheses and primary outcome measures. First, we are implementing a multi-level system quality improvement intervention to reduce racial disparities in blood pressure control via three multi-level interventions designed to standardize the measurement of blood pressure, provide patient care management services, and offer expanded provider education resources.

**Table 1 T1:** Project ReD CHiP’s specific aims, hypotheses and main outcome measures

**Specific aims**	**Hypotheses**	**Process and outcome measures**
To perform a multi-method, staged quality improvement intervention (better blood pressure measurement, patient care management and provider education) to increase guideline concordant hypertension care and to reduce racial disparities in blood pressure control.	• Better blood pressure measurement and better blood pressure data will lead to less clinical inertia and, ultimately, better blood pressure control and less racial disparities.	• % of patients with controlled BP and % of patients with uncontrolled BP with medication titration in the last 3 months
	• Each intervention will have an additive effect and the use of all three interventions will result in a higher percentage of patients receiving guideline-concordant hypertension care and a greater reduction in racial disparities than any single combination or any combination of two interventions.	• % of patients with controlled BP and racial disparity in controlled BP
	• The care management intervention will have greater net improvement in blood pressure control at the clinic level than the provider education intervention. The provider education will have an additive and greater effect when implemented after the care management intervention than when employed without the care management intervention.	• % of patients with controlled BP and racial disparity in controlled BP
To determine the association of organizational functioning and organizational cultural competence with guideline concordant hypertension care and racial disparities in blood pressure control.	• Clinics will reflect their local surroundings and clinics with a higher percentage of minority persons will have lower organizational functioning.	• % of patients with BP control, stratified by race, compared across clinics

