**Clinic Characteristics**						
Primary care providers, n	9	11	11	5	3	6
Patients, n	7,755	4,733	14,887	3,681	5,628	6,161
AA patients, %	65.6	90.1	23.3	18.4	17.7	20.2
White patients, %	28.0	4.4	68.9	77.7	73.3	72.6
AA patients with HTN, n	2,940	2,777	1,493	359	331	593
AA patients with uncontrolled HTN, %	33.1	38.8	29.7	40.1	40.5	42.8
White patients with HTN, n	705	80	4,209	1,362	650	1,477
White patients with uncontrolled HTN, %	29.2	33.9	24.3	34.9	37.1	30.6

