#### Statistical analysis plan

We will use Statistical Process Control (SPC) charting of measures over time to determine if there is a change at the system level after the implementation of the intervention and how long after implementation the change is evident [41,42]. SPC is a set of statistical methods based on the theory of variation that can be used to make sense of any process or outcome measured over time. Data will be visually inspected in a graphical display of a p-chart (for displaying proportion per time period). In this case, the x-axis will be each week of data collection (total of 24 weeks in the baseline data collection) and the y-axis will be the percent of patients seen that week with controlled blood pressure. We will distinguish normal variation from special causes (unusual changes in the pattern of data that can be assigned to a specific cause) using a range of statistically-driven tests, including: one value outside the control limits; two of three consecutive values above or below the mean and more than two standard deviations away from the mean; eight or more values falling above or below the mean; or six or more values in a row steadily increasing or decreasing (that is, showing a trend) [42].

We are also collaborating with health economists at our institution and other CPHHD centers to design and conduct a collection of cost-effectiveness analyses from health system, patient and societal perspectives, based on data from several of the ongoing interventions currently being studied by the CPHHD. We intend to capture program, patient and spillover healthcare costs, and cost offsets. The program perspective will determine the budgetary impact of implementing the interventions. Both patient and health system perspectives measure factors impacting individuals’ ability to adhere to the protocol. The success of interventions depends, in large part, on this. Additionally, interventions may have significant spillover effects, such as additional costs or cost offsets, on the healthcare system, which could impact the sustainability of the program within study sites and the likelihood of broader dissemination.

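### The primary outcome and the racial gap are charted over all patients seen each week, not patients with hypertension, so comparisons between races and clinics are confounded by prevalence

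*Protocol article*

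**What the plan says.** Under Outcome and process measures, the weekly data are aggregate percentages "with the denominator equal to the number of patients seen in clinic by all PCPs that week". What is counted against that total is patients who meet the Table 5 definition of the measure. The same section says that "the aggregate data will be stratified by these categories", race among them. Under Statistical analysis plan, the p-chart follows the same rule: "the y-axis will be the percent of patients seen that week with controlled blood pressure".

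Table 5 gives the primary outcome a threshold and no population: "Controlled BP defined as <140/<90 (or <130/<80 if DM or chronic kidney disease present". Table 1 pairs that percentage with the disparity measure: "of patients with controlled BP and racial disparity in controlled BP".

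Other parts use narrower populations. Table 2 has rows such as "AA patients with uncontrolled HTN", placed beneath counts of patients with hypertension. Several Table 5 rows name their own group: patients with hypertension, with hypertension and diabetes, eligible for care management, enrolled in it, or providers. The primary process measure, "with uncontrolled BP with medication titration in last 3 months", can be read either way; its wording in Table 1 reads more naturally as a percentage of the uncontrolled.

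**The concern.** The trial is about control of hypertension and its racial disparity. If everyone seen in the week is in the denominator, a patient who never had hypertension counts as a success. The percentage controlled then depends on two things: how many attenders have hypertension, and how well those patients are controlled. Only the second is the target of the interventions.

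Hypertension is more common among African American than white patients at these clinics, and its frequency differs between clinics. A racial gap would therefore remain on the chart after control among hypertensives had become equal. Clinics would also be ranked partly by case mix, which touches the cross-clinic comparisons of the second and third aims.

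**Working it through.** **Inputs (Table 2).** Patients per site, racial shares, hypertension (HTN) counts by race, and percent uncontrolled by race. The site counts add up to the stated total: 7,755 + 4,733 + 14,887 + 3,681 + 5,628 + 6,161 = 42,845.

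**Which denominator Table 2 uses.** At Site E, 40.5% of all African American (AA) patients would be 0.405 × (5,628 × 0.177) = 403, more than the 331 with HTN. The uncontrolled percentages must therefore be among patients with HTN.

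**Assumptions.** Patients without HTN are below threshold, and weekly attenders resemble the panel. The second is varied below.

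**Pooled prevalence P = HTN count / (site n × racial share), summed over sites.**
- AA: 8,493 / 15,738 = 54.0%
- White: 8,483 / 24,095 = 35.2%
- Both: 16,976 / 39,834 = 42.6%

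**Pooled share uncontrolled among HTN, U.**
- AA: 3,026 / 8,493 = 35.6%
- White: 2,424 / 8,483 = 28.6%
- Gap: 7.1 points from unrounded values

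**On the denominator as written, uncontrolled = P × U.**
- AA: 0.540 × 0.356 = 19.2%
- White: 0.352 × 0.286 = 10.1%
- Gap: 9.2 points from unrounded values
- Gap left if AA hypertensives had the white rate: (0.540 − 0.352) × 0.286 = 5.4 points

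**By site (gaps in points).**

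| Site | Gap among HTN | Gap on all patients | Left if control equal |
|---|---|---|---|
| A | 3.9 | 9.6 | 7.4 |
| B | 4.9 | 12.2 | 9.1 |
| C | 5.4 | 2.8 | 0.5 |
| D | 5.2 | 4.6 | 1.9 |
| E | 3.4 | 7.6 | 6.5 |
| F | 12.2 | 10.3 | 4.5 |

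On all patients (AA and white), Site E ranks best at 92.7% controlled. Among its hypertensives it ranks second worst, at 61.8%.

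**Change over time.** A 5-point gain in control among hypertensives moves the chart by 0.426 × 5 = 2.1 points. A 5-point rise in the share of attenders with HTN moves it the other way by 5 × 0.321 = 1.6 points, where 0.321 = 5,450 / 16,976 is the pooled share uncontrolled.

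**Titration, read literally.** Only 3,026 + 2,424 = 5,450 AA and white patients have uncontrolled HTN. Over AA and white patients this is 5,450 / 39,834 = 13.7%; over all 42,845 patients it is 12.7%. Complete titration would chart near 13–14%, and the ceiling would fall as control improved.

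**Sensitivity to attendance.** Suppose hypertensives are seen k times as often, so that P becomes kP / (kP + 1 − P).

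| k | Pooled gap, all patients | Left if control equal | Chart movement for a 5-point gain |
|---|---|---|---|
| 1 | 9.2 | 5.4 | 2.1 |
| 1.5 | 9.9 | 5.4 | 2.6 |
| 2 | 10.1 | 5.2 | 3.0 |
| 3 | 10.0 | 4.5 | 3.5 |

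The pooled result is stable. The shrinkage at D and F is not: at k = 2 their all-patient gaps (5.3 and 12.4) about equal the HTN gaps. The inflation at A, B and E and the shrinkage at C hold throughout.

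**The case against.** The strongest reply is that the general sentence is a summary in a condensed article, and that the rows of Table 5 govern. This stands for the rows that name a population. A reader might infer that every measure is computed over all attenders; the documents do not support that, and for titration they conflict rather than settle the matter. It does not rescue the primary outcome. Its row names no population, and the p-chart sentence states the all-patient denominator a second time. This is a stated rule, not a detail left to another document.

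A reader might also infer that the charts mostly track prevalence. That is too strong. At C, D and F most of the all-patient gap disappears once control is equal, and process control charts compare weeks within a clinic, where a stable prevalence largely cancels. What is left there is dilution and exposure to case-mix shifts, not a chart blind to change.

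The inputs are also imperfect. Table 2 gives panel counts and no threshold, and Table 5 sets a lower threshold for diabetes or kidney disease, so some patients without HTN would count as uncontrolled. These points limit the precision of the figures, not the mismatch of denominators.

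**Conclusion.** The denominator is wrong as written for the primary outcome and for the disparity built on it. On Table 2 panel counts, with patients without HTN taken as below threshold, the pooled gap is 9.2 points instead of 7.1, and about 5.4 points would survive equal control. Depending on the site, the gap is inflated (A, B, E) or shrunk (C, and at equal attendance D and F), so comparisons between races and between clinics are confounded by prevalence. Within a clinic the effect is chiefly dilution, to about 2.1 points per 5-point gain. The titration ceiling follows only from a literal reading that Table 1 resists; the passages need to be reconciled.

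**What to change.** State the populations and correct both sentences to match:
- Percentage controlled and racial disparity: patients with HTN seen that week.
- Titration: patients with HTN and uncontrolled blood pressure.
- Every other Table 5 row: the population that it names.

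Preferably identify HTN from the diagnosis code or medication, or from readings before roll-out. The Table 5 definition also admits patients on two raised clinic readings, and the measurement intervention can itself change those readings.

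The cost is a modified query on records that are already extracted retrospectively, and fewer patients per weekly point: about 43% of attenders at equal attendance, so wider control limits. The signal is undiluted in return. As an illustration with an assumed two-sided 0.05 level and 80% power, a 5-point gain among hypertensives needs 1,308 hypertensives per period. That is 1,308 / 0.426 ≈ 3,070 attenders, against 3,811 on the all-patient measure.

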**Disparities Tailoring**	**Patient**	• Poster messages and images reduce patient anxiety and promote trust	• Educational materials culturally and linguistically tailored	• Patient scenarios include individual and environmental determinants of disparities and demonstrate methods to address them
			• Motivational interviewing enhances patient engagement and addresses individual determinants of disparities	
			• Community resource guide addresses environmental determinants of disparities	
	**Provider and Staff**	• Re-training videos use local staff as role models	• Care managers enhance providers’ ability to address patients’ complex psychosocial needs by providing additional counseling and support	• Dashboard increases provider awareness of disparities
				• Communication skills training enhances provider participatory skills leading to increased patient trust and engagement
	**Clinic**	• Patient posters provide culturally and linguistically tailored communication	• Availability of phone contacts and flexible appointment times enhances access	• Financial incentives reward providers for reviewing disparities data
			• Financial incentives encourage providers to make referrals	

During the project’s development phase, physicians, nurse practitioners and MAs participated in baseline focus groups to discuss the feasibility and acceptability of the planned interventions. Research staff also attended clinic meetings and provider retreats and hosted webinars and workshops to hear feedback from individuals working in the clinics. At each site, organizational leaders as well as senior and practice level administrators completed semi-structured interviews with research staff. The results from these activities helped to shape the interventions. We will conduct follow-up focus groups and semi-structured interviews at the end of implementation to help increase the long-term effectiveness and sustainability of the interventions.

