We introduced the interventions in the context of other studies and other health system changes that were taking place at the clinics. Although we took steps in the development phase to incorporate site-level feedback, understand the organizational climate, and anticipate barriers to change, certain site level factors required us to make adjustments after initial implementation of the interventions. For example, in response to challenges with patient recruitment in the care management intervention at the first clinic, we adjusted our scheduling approach to better meet patient and provider needs. Instead of identifying patients only through the electronic patient registry, care managers also began to utilize direct referrals from providers. In particular, care managers found it more effective to focus their efforts on recruiting patients who are already present in the clinic for other appointments, instead of depending on reaching patients by phone. Responding to provider feedback, care managers now hold sessions with patients immediately before scheduled appointments with their PCP and also offer evening appointments once a week.

We underestimated the demand for additional site level support to assist with overcoming workflow and time management issues after the introduction of the automated devices in the blood pressure intervention. We also discovered the need to collect qualitative and quantitative data to determine if sites were adhering to the established protocol. Responding to these concerns, research staff members were able to offer time-saving techniques, monitor adherence to the protocol, and assist with device maintenance through weekly visits to each of the clinic sites. Additionally, we developed instructional videos to ensure that new clinic staff members are trained in the protocol for proper use of the automated devices.

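### The weekly outcome counts only patients whom PCPs saw that week, so a change in who is seen can be mistaken for, or can hide, a change in blood pressure control

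*Protocol article*

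**What the plan says.** In the protocol article, *Outcome and process measures* defines each weekly percentage with a "denominator equal to the number of patients seen in clinic by all PCPs that week". *Statistical analysis plan* repeats this for the p-chart of the primary outcome: "the y-axis will be the percent of patients seen that week with controlled blood pressure". Table 5 names the percentage with controlled blood pressure as the primary outcome.

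Under *Care management*, hypertensive patients "with their most recent blood pressure ≥140/≥90 mmHg are eligible for care management services". Care managers review the electronic registry "to identify eligible patients to outreach via telephone", and providers also refer patients. "Eligible patients receive three sessions totaling 120 minutes with an RD and/or a PharmD". Table 3 adds reimbursement to providers for reviewing their panels of eligible patients. Table 4 says of the same intervention: "Availability of phone contacts and flexible appointment times enhances access". The Discussion reports that "care managers now hold sessions with patients immediately before scheduled appointments with their PCP", and that recruitment moved towards patients already in the clinic.

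The planned strata are race/ethnicity, gender, age and chronic illness. Neither these nor the stated limitations deal with a change in who attends.

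**The concern.** A percentage taken over the patients seen in a week weights each patient by how often he or she attends. That does no harm while attendance patterns are stable. Here one of the interventions under test picks out patients by their value on the outcome (uncontrolled pressure) and contacts them, so the denominator may respond to the intervention itself.

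If uncontrolled patients come to PCPs more often, measured control falls with no patient worse. If they come less often, it rises with no patient better. The p-chart rules cannot tell either case from a real change.

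The article also ranks the interventions, expecting care management to improve control more than provider education. Only care management selects patients by uncontrolled pressure, so any distortion need not be equal on the two sides of that comparison.

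**Working it through.** **Inputs (Table 2, sites A to F).**
- African American patients with hypertension: 2,940; 2,777; 1,493; 359; 331; 593, sum 8,493. Uncontrolled: 33.1, 38.8, 29.7, 40.1, 40.5, 42.8%.
- White patients with hypertension: 705; 80; 4,209; 1,362; 650; 1,477, sum 8,483. Uncontrolled: 29.2, 33.9, 24.3, 34.9, 37.1, 30.6%.

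**Check of the article's own total.** 7,755 + 4,733 + 14,887 + 3,681 + 5,628 + 6,161 = 42,845, as stated. The article gives no sample size or power figure to rebuild.

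**Pooled baseline.** Uncontrolled: 3,025.9/8,493 = 35.6% (African American), 2,424.2/8,483 = 28.6% (white), 5,450.1/16,976 = 32.1% (both). Control is therefore 67.9% and the racial gap 7.05 points.

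**Formula.** Let u be the true uncontrolled share and r the chance that an uncontrolled patient sees a PCP in a given week, relative to other patients. Baseline r is taken as 1. Then

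measured control = (1 − u) / [(1 − u) + u·r].

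The article does not give r, so the values below are assumptions. They apply to every uncontrolled patient, and no patient's pressure changes.

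**Hypertensive patients only, u = 0.321.**

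| r | Measured control | Change (points) | Gap, same r in both races |
|---|---|---|---|
| 1 | 67.9% | 0 | 7.05 |
| 1.1 | 65.8% | −2.1 | 7.28 |
| 1.25 | 62.9% | −5.0 | 7.55 |
| 1.5 | 58.5% | −9.4 | 7.85 |

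The gap widens by 0.2, 0.5 and 0.8 points.

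**All patients seen, as the denominator is worded.** u ≈ 5,450/42,845 = 12.7%. The numerator covers African American and white patients only, so this share is approximate. Control starts at 87.3% and reads 86.2%, 84.6% and 82.1%, which are falls of 1.1, 2.7 and 5.2 points.

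**Gain that would be hidden (hypertensive patients).** Measured control stays at 67.9% if the true uncontrolled odds fall from 0.321/0.679 = 0.473 to 0.473/r. That is a real gain of 2.0, 4.7 or 8.1 points.

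**Opposite direction.** With r = 0.9, control reads 0.679/(0.679 + 0.321 × 0.9) = 70.1%, an apparent gain of about 2.2 points with no patient better.

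**Link to uptake.** Assume 3 PCP visits a year at baseline and 25% of uncontrolled patients enrolled. Then r = 1 + 0.25 × (extra PCP visits)/3. No extra visits gives 0.0 points, one extra gives r = 1.083 and −1.8 points, and three extra give r = 1.25 and −5.0 points. With 10% enrolled, one extra visit gives −0.7 and three give −2.1.

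**Would the chart react?** Assume 200 hypertensive patients seen per week and a normal approximation. The chance of eight consecutive weeks below the baseline mean within 24 weeks is 3.5% at r = 1, 42% at r = 1.1 and 97% at r = 1.25. For 100 to 400 patients per week it is 25 to 67% at r = 1.1 and 80 to 99.9% at r = 1.25.

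**Fixed panel.** If each registered patient counts once by latest reading, control stays at 67.9% and the gap at 7.05 points for every r.

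**The case against.** Much of the opposing case stands. The denominator counts patients seen by PCPs, whereas the sessions are with dietitians and pharmacists, so a session alone adds nobody to it. The Discussion places sessions before PCP appointments that were already scheduled and says recruiting patients present in the clinic worked better than telephoning. Both limit any shift in visit mix. The access statement in Table 4 concerns care management and is not said to mean PCP access. About 5,450 uncontrolled patients face 3 dietitians and 4 pharmacists, roughly 780 each, so a shift across all uncontrolled patients is unlikely to be large.

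A reader might infer three stronger claims that the article does not support.
- *The bias runs against the interventions.* It does so only if PCP visits by uncontrolled patients rise. Care managers who replace PCP follow-up would reverse it.
- *The dashboard brings patients back, or titration triggers extra PCP visits.* The article describes a dashboard showing percentages controlled, overall and by race, and describes no added PCP follow-up after titration.
- *The disparity result is badly distorted.* With an equal shift in both races the gap moves by less than one point. A shift confined to African American patients would give gaps of 9.3, 12.3 or 16.8 points, but outreach is not described as directed by race.

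It can also be said that the percentage controlled among patients seen is a coherent p-chart measure, and that sensitivity analyses belong in a fuller document. The second part does not answer the point: the article itself fixes the denominator, in two sections.

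**Conclusion.** The point holds as a weakness of measurement whose direction and size are unknown. The primary outcome as written mixes blood pressure control with the mix of patients attending, and one intervention selects patients by their control status. The illustrated falls rest on assumed visit shifts of 10 to 50% across all uncontrolled patients and on Table 2 shares for African American and white patients. They range from 2.1 to 9.4 points among hypertensive patients and from about 1.1 to 5.2 points with everyone seen in the denominator. They are not predictions, and zero is possible. Even so, at the assumed weekly volumes a shift at the low end would raise the chance of a special-cause signal several-fold. The planned chart alone could not show whether visit mix or control had changed. This should be addressed, but it does not invalidate the design.

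**What to change.** Keep the visit-based p-chart and prespecify two companions.

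1. **A panel series from the existing EMR registry.** Every 4 weeks, by clinic and race, report the percentage of hypertensive patients with a reading in a fixed look-back (for example 12 months) whose most recent reading is controlled, each patient counted once.
2. **A visit-mix chart.** Report PCP visits per hypertensive patient by prior control status and by intervention phase.

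State in advance that if the two outcome series disagree in either direction, the visit-based signal is read as possibly due to visit mix and is not attributed to blood pressure control alone. A rule allowing improvement to be claimed only when both series agree should be avoided, because it would not recover a real gain that the visit series hides.

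The cost is an extra registry query per period and a tabulation of visits. The panel series reacts more slowly, is autocorrelated, and still depends on who has a recent reading. Some early readings may predate the automated devices. It therefore supplements the visit series and does not replace it.
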